# Prehospital triage of patients with suspected acute stroke (PRESTO-2): protocol for a controlled before-and-after intervention trial

**DOI:** 10.1093/esj/aakag106

**Published:** 2026-09-07

**Keywords:** acute ischaemic stroke, digital health tools, EVT, healthcare organisation, prehospital triage

## Abstract

**Background:**

Prehospital triage of suspected stroke patients aims to reduce onset-to-groin time by eliminating the need for interhospital transfers for patients with ischaemic stroke caused by an LVO eligible for EVT, thereby improving long-term functional outcome. We aim to evaluate the implementation of a novel decision support tool, the Stroke Triage App (STA), which provides personalised triage advice by integrating stroke severity, onset time, GPS-based driving times, hospital-specific workflow metrics and time-dependent treatment effects.

**Study design:**

PRESTO-2 is a multicentre controlled before-and-after intervention trial. The study aims to evaluate the outcomes before and after implementation of prehospital triage with the STA in 1 acute-care region in the south-west of the Netherlands, compared with a control region. The STA is a smartphone-based application that uses an integrated decision model to estimate the probability of good functional outcome after 3 months (mRS score 0–2) under 2 strategies: transportation to the nearest primary stroke centre or transportation to the more distant intervention centre. Paramedics will use the STA for suspected stroke patients with a positive FAST test of 1 point or more.

**Study endpoints:**

The primary outcome is onset-to-groin time. Effects will be estimated using difference-in-differences linear regression analysis. Secondary outcomes include the onset-to-needle time, 3-month functional outcome, proportion of patients treated with IVT and EVT within guideline-recommended time windows, overtriage and undertriage, ambulance utilisation, compliance and adherence to triage advice.

**Summary:**

The PRESTO-2 study uses a pragmatic and efficient design for implementation studies, and is expected to provide insights into the optimisation of prehospital stroke care pathways and the challenges associated with integration of novel digital health technologies in existing clinical practice. These findings may inform scientists and clinicians to more efficiently design studies and organise stroke care pathways.

## Introduction

The effectiveness of both available acute reperfusion therapies for ischaemic stroke, intravenous thrombolysis (IVT) and endovascular thrombectomy (EVT), decreases as time elapses.^1–5^ IVT is available in most primary stroke centres (PSCs) and has a relatively broad indication, while EVT is only available in specialised intervention centres and is restricted to patients with LVO.^6–9^ Approximately one-quarter of patients with acute ischaemic stroke have a proximal intracranial LVO.^10^ The effect of IVT in this group of patients is small, but EVT is highly efficacious.^7^^,^^8^^,^^10^^,^^11^

Interhospital transfers are required for patients with an LVO stroke when they have first been transported to the nearest PSC, causing delay to initiation of EVT.^12^^,^^13^ Prehospital triage aims to eliminate these interhospital transfers by identifying these patients in the ambulance, allowing immediate transportation to an intervention centre. Various tools for detecting or estimating the likelihood of LVO have been developed to facilitate prehospital triage. Among these tools, prehospital stroke scales are the most widely used and investigated.^10^^,^^14^ When the total score of the prehospital stroke scale for a patient is above a defined cut-point, the patient is directly transported to the intervention centre.^15^^,^^16^ Prehospital stroke scales are implemented in several ambulance regions in the Netherlands and beyond to facilitate prehospital triage decision making, although a benefit of implementation of these scales on long-term functional outcome has not been unequivocally established.^17^ These scales do not account for essential regional characteristics, such as driving times to hospitals, workflow times within hospitals and transfer times between hospitals, while previous research showed that these are also important factors in determining the optimal transportation strategy besides stroke severity.^13^ These factors are combined with one of the best performing prehospital LVO detection scales, the Rapid Arterial oCclusion Evaluation (RACE) scale, into a decision support tool, the Stroke Triage App.^10^^,^^13^^,^^14^^,^^18^ The Stroke Triage App consists of an algorithm combining these factors in a multivariable decision model to aid ambulance staff in determining the best transport strategy for each individual patient.^19^^,^^20^

### Objectives

The primary objective of the PRESTO-2 study is to evaluate whether regional implementation of prehospital triage with the Stroke Triage App, compared with standard prehospital care without triage optimisation (ie, a drip-and-ship strategy), is associated with changes in onset-to-groin time in patients with ischaemic stroke due to LVO undergoing EVT, and with changes in onset-to-needle time in patients with ischaemic stroke without LVO. The secondary objective is to evaluate the implementation of the Stroke Triage App in the intervention region, in terms of logistics (over- and undertriage proportions and patient distribution), patient outcomes (proportion of patients treated with IVT and EVT) and user metrics (app usage, number of users and compliance among paramedics).

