### Data collection

Two separate datasets will be collected for the analysis of the 2 objectives. For the primary objective, data will be collected from the national stroke care quality registry (the Dutch Acute Stroke Audit [DASA] of the Dutch Institute of Clinical Auditing [DICA]). All Dutch hospitals report data regarding patient characteristics, process and outcome indicators to this registry annually. These registry data are used to prevent bias and disparities in the before-and-after intervention population cohorts in the intervention region and to control for time-dependent improvement in treatment times. To minimise the risk of double inclusions, patients receiving IVT will be included only if they were not transferred between hospitals. Patients undergoing EVT will be included solely from intervention centres. We will collect data including clinical characteristics (age, sex, type of stroke onset, date and time of stroke onset, NIHSS score and diagnosis), workflow and treatment indicators (date and time of presentation at Emergency Department, given treatment, door-to-needle time in case of IVT, door-to-groin time in case of EVT) and outcome indicators (mRS score after 3 months).

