### Outcome measures

#### Primary objective

The primary outcome measure for the primary objective will be the symptom onset or last known well time to groin puncture time (start of EVT) in patients with an ischaemic stroke with LVO who presented in the emergency department within 6 h from stroke onset. Secondary outcome measures for the primary objective will be the symptom onset to needle time (start of IVT) in patients who are treated with IVT, the percentage of patients with ischaemic stroke treated with IVT within the conventional guideline-recommended time window of 4.5 h after symptom onset or last seen well, the percentage of patients with ischaemic stroke treated with EVT within the conventional guideline-recommended time window of 6 h after symptom-onset or last seen well and the mRS score after 3 months.

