Within this context, this study has several notable strengths. The Stroke Triage App contains a decision model incorporating the most important aforementioned variables to calculate the probability of a good functional outcome for 2 transportation strategies for each individual patient. This personalised approach to prehospital triage allows for the Stroke Triage App to more easily be implemented in other regions with different regional characteristics. Prior to implementation of the Stroke Triage App, the effectiveness of the triage algorithm was established through modelling in a real-world cohort of suspected stroke patients in the region, supporting implementation of the application as a CE-compliant medical device.^21^ To evaluate the effectiveness of implementation of the Stroke Triage App, we considered utilising a randomised controlled trial design, but this approach would come with significant drawbacks. First, patient inclusion and randomisation to different transportation strategies would be a time-consuming process, adversely affecting the study population with treatment delays. Second, individual patient randomisation would likely have resulted in contamination of the control arm. After training in the use of the Stroke Triage App, paramedics may consciously or subconsciously incorporate the app’s triage logic into decision-making for patients allocated to standard care. This would diminish the contrast between intervention and control conditions and compromise the ability of the study to estimate the true effect of implementation. Third, the study aimed to evaluate the effectiveness of actual implementation of prehospital triage with the Stroke Triage App, including factors such as suboptimal paramedic compliance and non-adherence to the advice due to unforeseen circumstances. Finally, obtaining informed consent prior to or deferred consent after inclusion posed substantial logistical challenges, as previously described in the Methods section. Given that the Stroke Triage App was implemented as part of routine clinical care, we chose to utilise a pragmatic, non-randomised controlled before-and-after intervention design instead. This quasi-experimental design enables comparison with a control group, while the difference-in-differences analysis also adjusts for temporal trends in the improvement of treatment times for acute ischaemic stroke. One challenge in the study design was identifying a comparable control region without prehospital triage. Although distances between PSCs and intervention centres differed slightly between regions, these differences were stable over time and are therefore unlikely to bias the estimated intervention effect. As such, we expect the between-region differences before and after implementation to primarily reflect underlying temporal trends. Another challenge of this study was selecting an appropriate outcome measure. Onset-to-groin time in patients undergoing EVT reflects the potential benefits of the intervention, whereas onset-to-needle time in patients receiving IVT reflects its potential adverse consequences. A composite outcome was considered, but this was not feasible due to the expected high proportion of missing 3-month mRS scores in the DASA registry. Moreover, combining these time-based outcomes was methodologically challenging, as minutes gained in onset-to-groin time are not directly comparable to minutes lost in onset-to-needle time. To account for patients who may have forgone treatment as a result of triage decisions, we additionally report the proportion of patients receiving EVT and IVT.

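### The primary objective asks about onset-to-needle time in patients without LVO, but the outcome is defined in non-transferred IVT-treated patients, a mix that the app itself can change

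*Protocol article*

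**What the plan says.** All places are in the Protocol article.

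- **Objectives.** The primary objective has two parts: onset-to-groin time in LVO patients undergoing EVT, and an association "with changes in onset-to-needle time in patients with ischaemic stroke without LVO".
- **Outcome measures, Primary objective.** The population is different: "Secondary outcome measures for the primary objective will be the symptom onset to needle time (start of IVT) in patients who are treated with IVT". Nothing restricts it to patients without LVO.
- **Data collection.** To avoid counting patients twice, "patients receiving IVT will be included only if they were not transferred between hospitals". Patients having EVT are taken from intervention centres only.
- **Discussion.** The choice of outcomes is explained by saying that onset-to-groin time carries the possible benefit, "whereas onset-to-needle time in patients receiving IVT reflects its potential adverse consequences". Again there is no LVO restriction.
- **Data analysis plan.** The primary and secondary outcomes of this objective are analysed by difference-in-differences linear regression.

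**The concern.** Onset-to-needle time is the trial's measure of possible harm from bypassing a primary stroke centre, and its meaning depends on LVO status. The Introduction says that IVT has a small effect in LVO while EVT is highly efficacious. A later needle may therefore be offset by an earlier groin puncture in an LVO patient, but there is no such offset in a patient without LVO. The objective names the second group; the outcome definition does not isolate it.

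The no-transfer rule adds a second difficulty. It drops LVO patients who receive IVT at a primary stroke centre and are then sent on for EVT. It keeps LVO patients who receive IVT after direct arrival at an intervention centre. The app is intended to turn the first kind of patient into the second, so membership of the analysed set depends on the intervention. A result from this set could be read as the delay, or absence of delay, in patients without LVO, although that quantity was not estimated.

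**Working it through.** **Plan's own figure.** There is none to reproduce. The article gives no expected effect, standard deviation or power for onset-to-needle time; the sample size section concerns onset-to-groin time only.

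**Step 1: who is in each population.**

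| Patient given IVT | Objectives | Outcome measures and Discussion | After the no-transfer rule |
|---|---|---|---|
| No LVO, not transferred | in | in | in |
| LVO, taken directly to an intervention centre | out | in | in |
| LVO, IVT at a primary stroke centre, then transferred | out | in | out |

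The rule removes part of the LVO group but does not leave a non-LVO group. No sentence in the article closes the gap in the second row.

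**Step 2: effect in a mixed set.** Let s be the LVO share of the analysed set. With s constant, effect in the mix = (1 − s) × effect without LVO + s × effect with LVO. All inputs are assumed: a 5 min delay without LVO, and 0 to 20 min with LVO.

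- s = 10%: 0.90 × 5 + 0.10 × 0 = 4.5, to 0.90 × 5 + 0.10 × 20 = 6.5 min
- s = 25%: 0.75 × 5 + 0.25 × 0 = 3.75, to 0.75 × 5 + 0.25 × 20 = 8.75 min
- s = 40%: 0.60 × 5 + 0.40 × 0 = 3.0, to 0.60 × 5 + 0.40 × 20 = 11.0 min

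The mixed estimate can lie below or above the 5 min that the objective asks about.

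**Step 3: change in the mix.** Let p be the LVO share of all IVT-treated patients before the transfer rule, d the fraction of LVO patients arriving directly before implementation, and m the fraction of the remainder whom the app reroutes. For simplicity, every LVO patient taken to a primary stroke centre is transferred, and no patient without LVO is.

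- Share before: s0 = p·d / (1 − p + p·d)
- Direct fraction after: d′ = d + (1 − d)·m
- Share after: s1 = p·d′ / (1 − p + p·d′)
- Spurious difference-in-differences contribution, with no true effect in either group and a stable mix in the control region: (s1 − s0) × gap, where gap is the difference in mean onset-to-needle time between LVO and non-LVO patients

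The documents give none of p, d, m or the gap for this set. The Introduction's one-quarter is the LVO share of all acute ischaemic stroke. Assumed ranges are p 15–35%, d 30–50%, m 10–60%, and a gap of 30 min in either direction.

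| p | d | m | s0 | s1 | s1 − s0 | × 30 min |
|---|---|---|---|---|---|---|
| 0.15 | 0.50 | 0.10 | 0.081 | 0.088 | 0.007 | 0.22 |
| 0.25 | 0.50 | 0.33 | 0.143 | 0.181 | 0.039 | 1.16 |
| 0.25 | 0.30 | 0.33 | 0.091 | 0.150 | 0.059 | 1.78 |
| 0.35 | 0.30 | 0.60 | 0.139 | 0.279 | 0.140 | 4.21 |

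The first and last rows are the extremes of the grid. The shift is about 0.2 to 4.2 min, and its sign follows the sign of the gap.

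**Step 4: why the analysis does not remove it.** Difference-in-differences cancels fixed differences between regions and time trends common to both. A change in mix produced by the app occurs in one cell of four, the intervention region after implementation, so it stays in the interaction term with any true effect.

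**The case against.** The strongest reply is that the outcome section and the Discussion agree with each other, and only the sentence in Objectives differs. On that view the harm question is onset-to-needle time in patients receiving IVT, and rewording the objective settles the matter. This stands in part: rewording is a legitimate repair. It does not make the estimate a non-LVO effect, and it leaves the dependence on transfer untouched.

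Some stronger readings are tempting but unsupported:

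- **Rank.** A reader might infer that placing onset-to-needle time in the primary objective and then calling it secondary is a contradiction. It is not. The article labels it a secondary outcome measure for the primary objective, and the abstract is consistent: "The primary outcome is onset-to-groin time" and "Secondary outcomes include the onset-to-needle time".
- **All IVT-treated patients.** The no-transfer rule makes the set narrower than that.
- **Pooling must hide harm.** An LVO patient who bypasses a primary stroke centre also bypasses its needle and may have the larger delay. Step 2 shows that the bias can go either way.
- **The registry cannot identify LVO.** The extract is described as including "clinical characteristics (age, sex, type of stroke onset, date and time of stroke onset, NIHSS score and diagnosis". That list is not presented as exhaustive, and the diagnosis field may carry LVO status. How LVO is coded is a matter a protocol article may leave to its analysis plan.

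The unseen analysis plan may define one set. That would not remove the disagreement within the article.

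**Conclusion.** The concern holds as an inconsistency of population. The objective names patients without LVO. The outcome definition, read with the inclusion rule, gives a mixture of patients without LVO and directly arriving LVO patients, and the app can change that mixture in one cell only. The planned estimate is therefore not the effect stated in the objective.

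The inconsistency is certain from the text; the size is not. The range of about 0.2 to 4.2 min for the case-mix part rests wholly on the assumed p, d, m and 30 min gap, and its direction is open. The documents do not support saying that harm will be concealed, only that the non-LVO delay will not have been isolated.

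**What to change.** Before database lock, state one onset-to-needle population and use it in Objectives, Data collection, Outcome measures and the Discussion.

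- **Preferred.** Estimate onset-to-needle time in IVT-treated ischaemic stroke patients without LVO, in all four region-by-period cells, identified from a registry diagnosis or occlusion field if available. Report all non-transferred IVT-treated patients as a supportive analysis.
- **If only a treatment-based definition is possible** (no EVT and no transfer for EVT), label it as a proxy. It counts untreated LVO patients as non-LVO, and it depends on events that the app can change.
- **If the IVT-treated population is kept,** reword the objective to match, state the no-transfer restriction, and do not present the result as the delay in patients without LVO.

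The rank of the outcome need not change. Rewording costs only text. The preferred option costs a smaller cohort, hence a wider confidence interval, and some possible misclassification of LVO.

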## Methods

### Study design

The prehospital triage of patients with a suspected acute stroke (PRESTO-2) study is a prospective multicentre non-randomised controlled before-and-after intervention trial. The primary and secondary objectives require different analytical approaches and are therefore described separately below. For the primary objective, we will perform an implementation study using a controlled before-and-after intervention design with difference-in-differences analysis. We will use data from an intervention region and a control region. For the secondary objective, we will conduct a prospective observational cohort study.

### The Stroke Triage App

The decision model underlying the Stroke Triage App was derived from prior modelling studies and incorporates stroke severity assessed with the RACE scale, estimated symptom onset or last known well time, GPS-based transport times, interhospital transfer times and hospital-specific workflow metrics. For each patient, the app estimates the probability of good functional outcome (90-day mRS 0–2) under 2 transport strategies: transport to the nearest stroke centre (primary stroke centre or intervention centre) or direct transport to an intervention centre, bypassing closer primary stroke centres if appropriate.^19^^,^^21^ The app recommends the strategy with the highest probability of achieving an mRS score of 0–2 (Figure 1). The Stroke Triage App has been developed and is CE-certified under the Medical Device Regulation (MDR) class I software as medical device (EUDAMED UDI-DI: 08720892217905). Documentation regarding the MDR risk classification can be found in the Supplementary Materials.

**Figure 1 f1:**
[figure not shown]
Visual representation of the decision model forming the basis of the algorithm behind the Stroke Triage App.

### Study population

For the primary objective, we will include all adult patients (≥18 years) with a clinical hospital-confirmed diagnosis of ischaemic stroke who presented to the Emergency Department within 6 h from symptom onset in the 24 months before implementation (January 2022–January 2024) and 24 months after implementation (January 2024–January 2026) of the Stroke Triage App in both the intervention region and the control region. The intervention region consists of approximately 1.8 million inhabitants and 2 ambulance regions (Rotterdam-Rijnmond and Zuid-Holland Zuid), containing 2 intervention centres and 7 referring PSCs. The control region consists of approximately 2.8 million inhabitants and 4 ambulance regions (Zaanstreek-Waterland, Kennemerland, Amsterdam-Amstelland and Noord-Holland-Noord), containing 2 intervention centres and 9 referring PSCs, of which one closed in early 2023. No form of individualised triage was implemented in the control region during the study period, with patients being transported to the nearest IVT-capable stroke centre in accordance with national guidelines. The 2 regions are similar concerning degree of urbanisation and distances between hospitals (Tables 1 and 2).

**Table 1 TB1:** Description of the intervention region.

Hospital	Distance from intervention centre (km)	Estimated driving time (min) ^a^

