### Sample size calculation

Under the initial assumption that the Stroke Triage App would be used for all eligible cases and within the context of an implementation study running for 12 months, a power calculation rather than a sample size calculation was conducted. A mean (±SD) onset-to-groin time of 224.5 (±94.1) min was extracted from the Dutch MR CLEAN registry. Based on modelled data, where the Stroke Triage App algorithm has been applied to a prospectively collected cohort of prehospital suspected stroke patients, the mean effect of implementation of triage with the Stroke Triage App algorithm on the primary outcome measure (onset-to-groin time in patients undergoing EVT for ischaemic stroke with LVO) in the intervention region is estimated to be −31 min.^21^ We assumed a low intra-cluster correlation coefficient (ICC) of 0.01, as the primary outcome, onset-to-groin time, is substantially influenced by onset-to-alarm time. This interval is highly variable and largely determined by patient-specific and situational factors, such as stroke severity, aphasia, the presence of witnesses and time of symptom onset, which are largely independent of cluster membership. We also expected limited between-cluster variability. Public stroke-awareness campaigns are implemented nationally, acute stroke care is standardised through national guidelines and the study regions are comparable in terms of urbanisation. Together, the high within-cluster variability and limited between-cluster variability support the assumption of a low ICC in this study.

Based on previous stroke registry analyses, 96 EVTs annually in the intervention region would be required to reach a power of 80%. It was estimated that approximately 400 EVTs take place annually in the intervention region, which corresponds to a power of > 99% at a predefined alpha of 0.05.^22^ A sample size analysis for the secondary objective was not applicable.

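### The 6 h arrival window for the primary EVT cohort rests on a time the app can move; if it runs to the intervention-centre door, the primary effect is attenuated by roughly 5–20%

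*Protocol article*

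**What the plan says.** The Study population section restricts the cohort for the primary objective to ischaemic stroke patients "who presented to the Emergency Department within 6 h from symptom onset". The primary outcome repeats the limit: onset-to-groin time is assessed in patients "who presented in the emergency department within 6 h from stroke onset". Neither place says whether this means the first emergency department or the intervention centre's.

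The Data collection section states that "Patients undergoing EVT will be included solely from intervention centres". The listed workflow items are "date and time of presentation at Emergency Department, given treatment, door-to-needle time in case of IVT, door-to-groin time in case of EVT": one arrival time, hospital unspecified, and no clock time for groin puncture.

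The Introduction gives the mechanism: "Prehospital triage aims to eliminate these interhospital transfers by identifying these patients in the ambulance, allowing immediate transportation to an intervention centre". The Data analysis plan relies on difference-in-differences regression to deal with unobserved confounders and time-related differences.

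**The concern.** A cohort for a before-and-after comparison should be defined by something the intervention cannot change. Here membership depends on an arrival time, and changing arrival is what the app does.

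Take a patient who reaches a primary stroke centre 300 min after onset and, by transfer, the intervention centre at 390 min (an assumed interval). If the window runs to the intervention-centre door, this patient is excluded before implementation. Table 1 gives driving times of 10–49 min from referring hospitals to their intervention centre. If going direct adds at most that drive, arrival is no later than 300 + 49 = 349 min and the patient is included after implementation. With any plausible door-to-groin interval, the patient's onset-to-groin time lies far above the registry mean of 224.5 min. Such patients are missing from the before-period mean and present in the after-period mean.

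This happens only in the intervention region after implementation. Difference-in-differences removes stable regional differences and shared time trends. A change in cohort make-up caused by the intervention is neither. At stake is the size of the primary estimate.

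**Working it through.** **Inputs from the Sample size calculation and status sections.** Mean (SD) onset-to-groin time 224.5 (94.1) min; effect −31 min at full use; app use 33% at the interim, so 0.33 × (−31) = −10.2 min. The window is 360 min.

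**The plan's own figure.** The article quantifies nothing on this point. The nearest figure is power above 99% with 400 EVTs a year. For a plain comparison of 400 against 400: 31 / (94.1 × √(2/400)) = 31 / 6.65 = 4.66; 4.66 − 1.96 = 2.70; power 99.65%. That agrees, and it is not disputed here.

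**Assumptions, not in the article.** Log-normal or gamma times; share *s* of EVT patients transferred before implementation 40–75%; intervention-centre door-to-groin time *g* of 30–60 min if transferred and 60–75 min if direct; bypass makes first-hospital arrival 15 min later; no change in the control region, so it drops out of the contrast.

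**Model.** Let D be onset-to-groin time if taken directly, T = 1 if the patient would be transferred, and U = 1 if the app is used.
- Delay per transferred patient: d = 31 / s (for s = 0.5, 62 min).
- Before: Y0 = D + T·d. After: Y1 = D + T·(1 − U)·d.
- D has mean 224.5 − 31 = 193.5 and variance 94.1² − s(1 − s)d², so Y0 has the registry mean and SD. For s = 0.5: 8854.8 − 0.25 × 3844 = 7893.8, SD 88.8.
- Intervention-centre arrival: A = Y − g.
- Restricted effect: mean(Y1 | A1 ≤ 360) − mean(Y0 | A0 ≤ 360).

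**Results** (2 million simulated patients per scenario; effects in min):

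| Shape, s, g transferred/direct | App use | No restriction | 6 h to intervention-centre door | 6 h to first door |
|---|---|---|---|---|
| Gamma, 40%, 30/60 | 100% | −31.0 | −24.1 (22% smaller) | −31.5 |
| same | 33% | −10.2 | −8.1 (21% smaller) | −10.4 |
| Log-normal, 50%, 45/75 | 100% | −31.0 | −25.8 (17% smaller) | −31.5 |
| same | 33% | −10.2 | −8.6 (16% smaller) | −10.4 |
| Log-normal, 75%, 60/60 | 100% | −31.0 | −27.9 (10% smaller) | −31.9 |
| same | 33% | −10.2 | −9.3 (9% smaller) | −10.5 |

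The first and third scenarios are the extremes of the grid. With the window at the intervention-centre door, 3.4–5.4% of EVT patients are excluded before implementation. After it, 1.2–2.6% are excluded at full use and 2.8–4.5% at 33% use.

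**Second set of assumptions.** This builds time forward: onset to first door log-normal with median 70–100 min and log-SD 0.7–0.8; 50–65% first taken to a primary stroke centre; transfer adds 75–120 min; door-to-groin 50 min. It gives 5–18% attenuation: −31 becomes −25.4 to −29.6, and −10.2 becomes about −8.5 to −9.8.

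**Taken together:** roughly 5–20%. At 33% use, 0.05 × 10.2 = 0.5 min to 0.20 × 10.2 = 2.0 min.

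**First-door reading.** Bypass delays first arrival slightly, so a few late patients drop out of the after period. The estimate is then 1–3% too large.

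**Precision.** The window also trims the spread: the before-period SD falls from 94.1 to about 71–82 min. In the middle scenario at 33% use, effect over SD is 8.6 / 75.9 = 0.11 with the window and 10.2 / 94.1 = 0.11 without it.

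**The case against.** The strongest reply is that attenuation depends on a premise the article does not state. Saying which centres supply the EVT records does not settle which arrival time those records hold; that lies in the registry's data definitions. A reader might infer that the primary effect is certainly attenuated. The text does not support that, because on the first-door reading the bias is small and points the other way. This stands, and the point is conditional for that reason. The intervention-centre reading remains the natural one: the record is that centre's, and with no groin clock time listed, onset-to-groin time would be built as arrival minus onset plus "door-to-groin time in case of EVT", which needs both parts to refer to the same door.

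A reader might also infer lost power. Nothing shows it: the spread shrinks along with the effect, and attenuation is conservative.

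Nor is it shown that the percentage treated with EVT within 6 h is distorted. Its denominator is described as patients with ischaemic stroke, not EVT recipients.

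Finally, the choice of timestamp and sensitivity windows may be in the supplementary analysis plan, which is not at hand. That could resolve the ambiguity, but the inclusion rule is stated in the article and conditions on arrival under either reading. Reporting treated proportions, as the Discussion proposes, addresses forgone treatment and not this selection.

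**Conclusion.** The concern holds in conditional form. Primary-cohort eligibility depends on an arrival time that the app can move, in the intervention region after implementation only, and difference-in-differences does not correct for it. If the 6 h runs to the intervention-centre door, the primary estimate is attenuated by roughly 5–20%, or about 0.5–2 min of a 10.2 min effect at 33% use. If it runs to the first door, the bias is about 1–3% away from the null. The direction rests on which door is meant; the size rests on assumed transfer shares, delays, door-to-groin times and distribution shape. It is a modest bias in the primary estimate, worth correcting because the correction is cheap, and it does not invalidate the design.

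**What to change.** 1. State which arrival defines the 6 h, and use first-hospital arrival where the intervention-centre record holds it. The app moves this time too, but only slightly.
2. In either case, pre-specify a difference-in-differences analysis of onset-to-groin time in all EVT-treated patients without the arrival restriction, for example within 24 h of onset or last known well, the horizon already used for the secondary objective. Report it alongside the 6 h analysis.
3. Report the numbers excluded by the 6 h rule by region and period.

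Widening the window to 8 h is not enough on its own: about 1–8% attenuation remains across the assumptions tried.

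The cost is a registry filter, a few sentences and a little more analysis. The unrestricted analysis has more variance and a somewhat different, later population, so it complements the 6 h analysis and need not replace it. The Data analysis plan places database closure and analysis after submission of the protocol. If the outcome analysis has already been run, the added analysis should be labelled post hoc.
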